**Figure 4 fig4:**
[figure not shown]
Locations of the SA group.

#### Routine treatment

2.6.3

The MA and SA groups receive 4 weeks of routine basic treatment, including nutritional support, and nursing care (including positioning, oropharyngeal care, and pressure ulcer prevention).

### Outcomes

2.7

At baseline, 2 and 4 weeks post-treatment, and at the 3-month follow-up, several experienced and trained third-party personnel are blinded to the outcome indicators. Simultaneously, sEMG data are collected by a specialized, trained rehabilitation therapist who is not involved in the design, and the RMS, iEMG, and MF of the affected upper limb core muscle group are compared before and after treatment.

#### Primary outcome

2.7.1

The primary outcome is the Fugl–Meyer Assessment (FMA), which is used in clinical settings and research to assess motor deficits and recovery in individuals post-stroke (21) and is categorized into the FMA-UE (UE, upper extremity) specifically for assessing upper extremity function. The FMA-UE, one of the most widely used and recognized clinical assessment tools for evaluating upper limb motor function, has a total of 33 items and is divided into three scoring grades according to task completion degree (0, 1, and 2 points respectively), with a total score of 66 points; the higher the patient’s score, the better the motor function because of the quantitative indexes, which make its assessment detailed, reliable, and sensitive. According to the study, the change in FMA-UE between the two groups is the minimum clinical difference (MCID), equal to 5.2 (22).

#### Secondary outcomes

2.7.2

Secondary outcomes include the Motor Status Scale (MSS), Action Research Arm Test (ARAT), Motor Assessment Scale(MAS), self-rated anxiety scale (SAS), and self-rated depression scale (SDS) scores.

The MSS scale is divided into several parts including the shoulder, elbow and forearm, wrist, and hand. It includes five major categories: shoulder movement, elbow and forearm movement, wrist movement, hand movement, and upper limb activities based on hand function, with a total of 29 sub-items and a maximum score of 82. The higher the score, the better the function. MSS is an upper limb motor function assessment method designed by Asien and others based on the upper limb motor section of the Fugl-Meyer Assessment (FMA-UE), addressing the FMA’s lack of evaluation for individual finger motor function. The MSS assessment includes isolated movements that make up complex movements, allowing for a more sensitive reflection of functional impairments and treatment effects (23).

The ARAT scale provides a comprehensive and standardized method to assess upper limb function. It assesses upper limb movement through four basic movements: grasping (six items), griping (four items), pinching (six items), and gross motor (three items). Each item is rated on a 4-point scale of 0 for failure to 3 for normal completion out of 57 points. The evaluation of limb dysfunction caused by cerebral cortical injury involves effectively assessing limited arm movements by evaluating the patient’s ability to manipulate objects of different sizes, weights, and shapes (24).

The MAS score is highly correlated with the FMA and is used to evaluate muscle spasms and muscle tension by observing the degree of muscle tension in different postures to accurately assess motor function (25). The nine items of the scale are scored from 0 to 6 points, in which the total score of the whole-body muscle tension is not included in the total score, and the total score of the eight items is 48 points. Higher scores indicate better motor function. Movement disorders are classified as mild (> 33 points), moderate (17–32 points), or severe (0–16 points).

The SAS is used to assess the subjective feelings of patients with anxiety. It is a 4-point self-rating scale containing 20 items. Higher scores indicate more severe symptoms (26).

The SDS is a tool for individual self-assessment of depressive symptoms (27). It contains 20 items divided into positive scores (1–4 points) and reverse scores (4–1 points). The cutoff value of the standard scores is 53 points; 52–62 is classified as mild depression, 63–72 as moderate depression, and >72 as severe depression.

#### Other outcomes

2.7.3

sEMG is a technique for recording the bioelectrical signals of the neuromuscular system during muscle activity (13), which can quantify muscle functional status. It was recorded using a 10-channel multi-lead 060525001 Myotrac3 surface electromyograph (THOUGHT, Canada). The evoked potentials of the core upper limb muscle groups (including pectoralis major, deltoid, biceps brachii, triceps brachii, brachioradialis, etc.) defined by neuroanatomy experts were collected. The specific indicators include the root-mean-square value (RMS) and integrated electromyography value (iEMG) of the time-domain indicators, which quantify the overall muscle activation strength from the perspectives of transient intensity and cumulative loading, respectively. Frequency domain indicators include the median frequency (MF), defined as the frequency point corresponding to 50% of the energy accumulation in the spectrum, to infer muscle fiber conduction velocity (MFCV), which is used to assess muscle fatigue (28). Before collection, evaluators need to undergo standardized training to regulate the movement patterns of the core muscle groups; then the evaluators guide the patients in exercise to practice and master the standardized movement methods; secondly, before collection, the signal acquisition parameters of the instrument need to be pre-tested to ensure parameter stability. The specific operation is as follows: Inform the patient before the test to perform relevant actions according to sEMG. The patient is in a sitting position before applying the electrode sheet, local hair removal is carried out on the site where the electrode sheet is to be applied, the skin surface is polished with a special sanding pad, and then wiped with an ethanol cotton ball to remove the skin cuticle, reduce the contact resistance between the electrode and the detection surface, and protect the electrode to avoid movement and avoid errors as much as possible. After completing the electrode affixing, the electromyographic signal becomes stable, and detection begins. According to the machine’s instructions, the doctor and patient cooperate to complete the corresponding active and passive movements. Each movement lasts for 15 s, followed by a 5-s rest. Each movement is repeated 3 times as one set, with a 1-min rest after each set. The middle 10 s of the electromyographic signal for each movement is used for analysis.

#### Blinded index

2.7.4

Participants were asked to guess the type of acupuncture they received at the end of the acupuncture treatment. A third party recorded the data, and statisticians used the SAS macro %BBI2 for visual analysis to assess the success rate of blinding in the randomized controlled trial (29). The environment for this macro is based on SAS V.9.4 (SAS Institute, Cary, North Carolina, United States). For each group (e.g., MA and SA), the BBI is calculated as:

$${\mathrm{BBI}}_{n}=(2•T_{n}^{2}-1)•(\frac{N_{n,\text{correct}}+N_{n,\text{wrong}}}{N_{n,\text{total}}})$$

$$T_{n}^{2}=\frac{N_{n,\text{correct}}}{N_{n,\text{correct}}+N_{n,\text{wrong}}}$$

$$N_{n,\text{total}}=N_{n,\text{correct}}+N_{n,\text{wrong}}+N_{n,\text{unknown}.}$$

BBI ∈ [−1, 1], with 0 indicating a random guess; BBI ∈ [−0.2, 0.2] indicates a successful blinding.

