**Figure 1 fig1:**
[figure not shown]
Participants flow chart. CONSORT 2025 Flow charts: Flow charts of the two groups at each stage of the trial (e.g., recruitment, intervention allocation, follow-up, and data analysis). Acu, Manual-Acupuncture; Sham Acu, Sham-Acupuncture.

**Table 1 tab1:** Study design.

	STUDY PERIOD						
		Allocation	Treatment				Follow-up
TIMEPOINT**	*-t_1_*	0	*t_1_*	*t_2_*	*t_3_*	*t_4_*	*t_5_*
		Baseline	Week1	Week2	Week3	Week4	3-months
ENROLMENT							
Eligibility screen	X						
Informed consent	X						
NIHSS	X						
Demographic information	X						
Random Allocation		X					
INTERVENTIONS:							
MA							
SA							
ASSESSMENTS:							
FMA		X		X		X	X
MSS		X		X		X	X
ARAT		X		X		X	X
MAS		X		X		X	X
SAS		X		X		X	X
SDS		X		X		X	X
sEMG		X				X	
Biochemical indicators		X				X	
Blinding Index		X				X	
Adverse events			X	X	X	X	X

Study schedule of enrollment, interventions, and assessments. The template is from the SPIRIT 2013 statement. HA, hand acupuncture; SA, shame acupuncture; FMA-UE, Fugl-Meyer assessment upper extremity; MSS, Motor Status Scale; ARAT, Action Research Arm Test; MAS, modified Ashworth scale; SAS, Self-Rating Anxiety Scale; SDS, Self-Rating Depression Scale.

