### Sample size

2.5

The sample size calculation for this study was based on the primary outcome measure, the FMA-UE score. According to preliminary pilot results, the mean difference (MD) in FMA-UE scores between the acupuncture and control group after treatment was 11.5, with a standard deviation (SD) of 10.4. Meanwhile, the minimal clinically important difference (MCID) for the Chinese version of the FMA-UE is 4.6. This study was a superiority design, using PASS 15.0 software for sample size estimation. An independent samples t-test was employed, with a significance level set at *α* = 0.05 and power *β* = 0.8. It is estimated that the acupuncture group must reach the MCID value compared to the sham acupuncture group to be clinically meaningful. Therefore, the superiority margin is set equal to the MCID value of 4.6. The minimum sample size calculated is 58 cases. Considering a 20% dropout rate, the final sample size was determined to be 74 cases (37 cases each in the MA and SA groups).

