### Data processing and statistical analysis

2.10

Data analysis was performed by qualified personnel not involved in the study using the Modified Intention-to-treat (mITT) principle. mITT was defined as participants who were randomized, received at least one treatment, and were statistically analyzed using the SPSS (IBM SPSS Statistics, Version 26.0) software. The significance level was set at 5%. Continuous variables that conform to the normal distribution are represented by mean ± standard deviation (x ± s), and non-normal continuous variables are represented by median and quartile [M (P25, P75)]. Categorical variables are expressed as frequency (percentage) using a chi-square or Fisher precision test. For primary and secondary outcomes, an independent sample T-test was used to compare groups if normal distribution and homogeneity of variance were met; otherwise, the Mann–Whitney *U* test was used. Intragroup comparisons were performed using the paired sample T-test. According to missing outcome data, the last observation carried forward (LOCF) method or multiple interpolation was used to fill in the missing values. In addition, sensitivity analyses were performed to clarify the robustness of the results by comparing the conforming protocol analysis set (PPS) analysis with the ITT analysis set. The data obtained by sEMG were analyzed with the main outcome, FMA-UE, using Person/Spearman correlation analysis. Finally, we calculated the BI index to evaluate the success of blinded implementation.

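### The ±0.2 rule for the blinding index ignores sampling error, sign and the joint pattern of the two arms, so with 37 per arm it can misjudge blinding in either direction

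*Protocol article*

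**What the plan says.** Section 2.7.4 (Blinded index) gives the timing: "Participants were asked to guess the type of acupuncture they received at the end of the acupuncture treatment". It sets the level of calculation: "For each group (e.g., MA and SA), the BBI is calculated as", followed by a formula that counts correct, wrong and unknown answers. It then gives the scale, "with 0 indicating a random guess", and the criterion, that a BBI within [−0.2, 0.2] "indicates a successful blinding".

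Section 2.10 gives the purpose: "Finally, we calculated the BI index to evaluate the success of blinded implementation". Section 2.5 fixes the number of possible guesses: "the final sample size was determined to be 74 cases (37 cases each in the MA and SA groups", after a 20% allowance for dropout on a minimum of 58.

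Table 1 marks the row "Blinding Index" at baseline and at week 4.

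The article mentions no confidence interval for the index. It does not treat positive and negative values differently and does not say how the two arms combine into one conclusion.

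**The concern.** The team's own sham device and the blinding it is meant to secure are central to the trial's argument. The Introduction and Discussion both rest the separation of specific from non-specific effects on it. The index is the only stated check on whether the blinding worked.

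A fixed cut on a point estimate is a weak check for three reasons.

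- **Sampling error.** An index based on at most 37 answers moves by more than 0.2 by chance alone quite often.
- **Sign.** In the sham arm a negative index means that most participants wrongly believe they had real needles. The band scores this the same as participants correctly identifying their treatment.
- **Joint pattern.** If the sham is convincing, many participants in both arms may answer 'real'. That gives a positive index in the acupuncture arm (MA) and a negative one in the sham arm (SA). The guess is then unrelated to allocation, yet both arms can lie outside the band.

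The report could therefore question a sound blind or endorse a broken one.

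**Working it through.** **Inputs.** From the article: 37 per arm (29 per arm before the dropout allowance), the band [−0.2, 0.2], and 0 for random guessing. Assumed, because the article gives no figures: the share of unknown answers and the share answering 'real'. Both are shown as ranges. The article states no error rate for the rule, so there is no figure of its own to reproduce.

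**The index.** With c correct, w wrong and n total answers, the printed formula reduces to BBI = (c − w)/n. Without unknown answers, BBI = 2c/n − 1, and at random guessing its standard error is 1/√n.

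**Precision at n = 37.** SE = 1/√37 = 0.164. The half-width of the band is 0.2/0.164 = 1.22 SE, so the whole band spans about 2.4 SE. The half-width of a 95% CI near 0 is 1.96 × 0.164 = 0.32. No possible result has its whole (Wald) interval inside ±0.2.

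**Random guessing.** BBI is inside the band only for 15 to 22 correct guesses (−0.189 to +0.189); 14 or 23 give ∓0.243. From the exact binomial with p = 0.5:

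- One arm inside: 0.812; outside: 18.8%.
- Both arms inside: 0.812² = 0.660; at least one outside: 34.0%.

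Trials with at least one arm outside, by share of unknown answers:

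| Guesses per arm | 0% | 10% | 20% | 30% | 50% |
|---|---|---|---|---|---|
| 37 | 34.0% | 35.1% | 30.8% | 26.1% | 15.5% |
| 29 | 46.0% | 48.6% | 44.5% | 39.6% | 27.4% |

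**Same share r answering 'real' in both arms.** Without unknown answers, the expected BBI is 2r − 1 in MA and 1 − 2r in SA. The two sum to zero, which is what a guess unrelated to allocation gives. At r = 0.70 they are +0.4 and −0.4. At n = 37:

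| r | One arm inside | At least one outside |
|---|---|---|
| 0.55 | 0.733 | 46.2% |
| 0.60 | 0.530 | 71.9% |
| 0.65 | 0.292 | 91.5% |
| 0.70 | 0.113 | 98.7% |

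With 20% unknown answers and 70:30 among those who guess, the last figure is 96.2%.

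**Error in the other direction.** An arm with a true BBI of 0.3 (p = 0.65) lies inside the band with probability 0.292. At a true BBI of 0.2 the probability is 0.530.

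**Would a confidence-interval flag repair this?** Take the rule 'flag an arm only if its 95% Wald CI lies above 0'. At n = 37 it flags a true BBI of 0.3 in 44.5% of arms and so misses about 55%, against 29% inside the printed band. At a true BBI of 0.2 it misses 78%, against 53%. A CI that includes 0 is therefore not evidence of blinding.

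**Timing.** Section 2.7.4 asks for the guess only at the end of treatment. Table 1 also marks the index at baseline, before any needling, when there is no treatment experience to guess from.

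**The case against.** The strongest reply is that the article says less than the criticism needs. It calls values inside the band successful. It never says that values outside mean failure, or that both arms must be inside. A reader might infer that a third of perfectly blinded trials would be declared unblinded. The documents do not support that without conditions: the 34% needs both readings, and the single-arm figure is 18.8%. Half of those arms have a negative index, so only 9.4% exceed +0.2.

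A reader might also infer that the rule almost always fails when both arms believe they had real needles. That depends on the share. It holds at about 70% or more, whereas a slight lean of 55–60% gives 46–72%. The article gives no guess shares.

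Intervals and a joint display may also appear in the analysis plan, which is not shown, or in the output of the SAS macro that section 2.7.4 names for visual analysis. That is possible. The band is nevertheless printed in the article as the criterion, and a display does not change how it reads.

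No endpoint, analysis set or test depends on the index. This is correct and limits the weight of the point. Whether to ask for a guess earlier, for instance after the first session, is a design preference. An early question may itself raise suspicion, and only the mismatch between Table 1 and the text is a defect.

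**Conclusion.** The point stands in a limited form. The printed criterion is a cut on a per-arm point estimate that ignores sampling error, sign and the joint pattern, and 37 per arm is too few for it to separate good from poor blinding reliably.

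The false-alarm rate under random guessing is 18.8% per arm. It is 34% per trial if both arms must be inside and outside counts as not successful, with a range of about 15% to 49% over the assumed unknown shares and 29 to 37 guesses per arm. The figures for a shared belief in real needles (72% at 60%, 99% at 70%) use the same reading with no unknown answers. The 29% chance that an arm with a true BBI of 0.3 is inside applies to a single arm at n = 37 with no unknown answers.

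The consequence is confined to the statement about blinding, which affects how the primary result is interpreted but not its analysis. The change should be made, but it is not critical to the trial's validity.

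**What to change.** In section 2.7.4:

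- Remove the pass/fail reading of the point estimate. Report BBI in each arm with its 95% CI, together with the counts of correct, wrong and unknown answers.
- Interpret the two arms jointly and with their sign. Read MA positive with SA negative as both arms believing they had real needles, not as unblinding.
- State the limit of the evidence. With a CI half-width of about 0.32, the trial can neither confirm a BBI within ±0.2 nor rule out moderate unblinding, so a CI that includes 0 is not proof of blinding. Do not replace the band with a flag based only on the CI lying above 0.

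Reconcile Table 1 with section 2.7.4: either remove the baseline mark or explain what is collected then.

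The cost is a few sentences and one table entry, with no new data. The small downside is a less categorical verdict on blinding.

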### Adverse events and safety

2.8

#### Definition and handling of adverse events

2.8.1

Any incidents, symptoms, signs, or abnormal examination results occurring between the intervention and the last follow-up. Common needle-related adverse events (AE) include broken needles, dizziness, and infection. Serious adverse events (SAE) refer to any experience or condition that poses significant harm to the patient or contraindicates continued treatment, such as stroke recurrence or organ damage. During the research process, as soon as a patient expresses discomfort, the physician will immediately stop treatment assess the patient’s signs, symptoms, type, and extent of discomfort, and take appropriate measures to protect the safety of the subject. The patient will be followed up until the condition stabilizes after the adverse event occurs.

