**Methods:**

In this prospective, principal-investigator-blinded randomized controlled trial, 74 patients who meet the inclusion criteria are randomly assigned to the acupuncture and sham acupuncture groups in a 1:1 ratio using a central randomization system. The patients receive the same routine basic treatment. The core acupoints selected in the acupuncture group are GV20 (Bai hui), DU14 (Da zhui), and LI11 (Qu chi). Six non-meridian acupuncture points are selected for the sham acupuncture group. The treatment cycle lasts for 4 weeks, five times per week, for 20 treatments. The Fugl–Meyer Upper Limb Assessment scale score is used as the main outcome. Secondary outcomes include the Motor Status Scale, Action Research Arm Test, Motor Assessment Scale, Self-rating Anxiety Scale, and Self-rating Depression Scale scores. Simultaneously using sEMG as an auxiliary efficacy indicator.

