#### Withdrawal criteria

2.2.3

(1) Withdrawal as decided by the investigator:

① During the study, the participant has certain comorbidities, complications, or pathological changes that make it unsuitable to continue the study.② In the study, the participant has poor compliance, which may affect the evaluation of effectiveness and safety.③ The participant breaks the blindness or exposes the blinded data in an emergency.④ Adverse events and serious adverse events occurred, making a participant unsuitable to continue to receive the study.

(2) Withdrawal from the study.

According to the provisions of the informed consent, participants have the right to withdraw from the study midway, or the participants may not explicitly withdraw from the study, but may no longer receive medication and testing, and lose follow-up (which is also classified as a “withdrawal,” called “drop”). The reasons for withdrawal, such as poor efficacy, intolerance to certain adverse effects, inability to continue the clinical study, economic factors, and failure to explain the reasons for the loss of visits, should be understood as much as possible and recorded.

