#### Security analysis

2.8.3

AEs are classified and reported according to common AE evaluation criteria.

Incidence = (number of patients with AE/total number of patients) × 100%

Fisher’s exact test is used to compare intergroup incidence.

Individual list description risk ratio (RR), and confidence interval (CI) calculations are performed for SAEs. Comprehensive recording and analysis ensure subject safety and data integrity, in order to complete statistical analysis and help investigators understand the potential effects of acupuncture.

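### The SAE definition in 2.8.1 lets a bar to further treatment alone make an event serious, which mixes seriousness with discontinuation and lapses when treatment ends at week 4

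*Protocol article*

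**What the plan says.** The relevant statements are spread over four parts of the protocol article.

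- **Seriousness (2.8.1).** An SAE is "any experience or condition that poses significant harm to the patient or contraindicates continued treatment, such as stroke recurrence or organ damage". Two conditions are joined by *or*: a harm limb and a treatment-continuation limb.
- **Ordinary needle events (2.8.1).** "Common needle-related adverse events (AE) include broken needles, dizziness, and infection". The same section says that "as soon as a patient expresses discomfort, the physician will immediately stop treatment", after which the patient is assessed. No seriousness label is attached to that stop.
- **Observation window (2.8.1 and Table 1).** Adverse events are those "occurring between the intervention and the last follow-up". Table 1 schedules them at weeks 1 to 4 and at the 3-month follow-up.
- **Treatment period (Abstract, Methods).** "The treatment cycle lasts for 4 weeks, five times per week, for 20 treatments".
- **Withdrawal (2.2.3).** Investigator criterion (1)④ reads: "Adverse events and serious adverse events occurred, making a participant unsuitable to continue to receive the study". Reasons for a participant's own withdrawal include "intolerance to certain adverse effects, inability to continue the clinical study".
- **Analysis (2.8.3).** "Individual list description risk ratio (RR), and confidence interval (CI) calculations are performed for SAEs".
- **Needles (2.6.1 and 2.6.2).** The MA needle is inserted 10–30 mm. The sham (SA) needle is blunt and does not pierce the skin, but it is pressed on to produce a tingling feeling.

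**The concern.** How serious an event is and whether it ended treatment are different attributes of that event. The definition merges them, because the continuation limb is enough by itself. Three things follow.

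First, an event with a minor outcome that nonetheless rules out further needling meets the definition. Second, the criterion changes part-way through the window: two limbs during treatment, one afterwards. The remaining limb has two examples and no outcome criteria. Third, 2.2.3 assumes a class of non-serious events that end participation, and 2.8.1 leaves little room for it.

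What is at stake is the SAE comparison in 2.8.3, and safety is one of the two stated aims of the trial (2.1). Events caused by penetration can arise only in MA, so any reclassification need not cancel between arms. The acupuncturists know the allocation (2.4). Section 2.3 also sends group information to the investigator, and 2.8.2 has the investigator record adverse events. The article therefore does not rule out that a discretionary rule is applied by someone who knows the arm.

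**Working it through.** The plan states no SAE rate and no figure that depends on this definition, so there is nothing to reproduce. The check is mainly textual, with one illustration.

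**1. Two rules on one event.** Take an event during weeks 1 to 4 with a minor outcome, judged to rule out further treatment.

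| Rule | Question asked | Result |
|---|---|---|
| 2.8.1, harm limb | Does it pose significant harm? | No |
| 2.8.1, continuation limb | Does it rule out further treatment? | Yes, so SAE |
| 2.2.3 (1)④ | Does an AE or an SAE make the participant unsuitable to continue? | Yes, and it may be a plain AE |

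Criterion ④ names both classes, so it presupposes that some non-serious events end participation. Under 2.8.1, if the reason is that treatment is ruled out, the event is already serious. Two recorders could code the same patient differently, and the article does not settle which coding applies.

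**2. The window.** Treatment lasts 4 weeks. The article does not say whether the 3-month visit is counted from baseline or from the end of treatment. Taking 3 months as about 13 weeks:

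- counted from baseline: (13 − 4) / 13 = 9/13 = 69% of the window has no treatment to rule out;
- counted from the end of treatment: 13 / (13 + 4) = 13/17 = 76%.

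On either reading, only the harm limb operates for most of the window.

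**3. Sensitivity of the SAE risk ratio.** Input from 2.1: 37 per arm. Assumptions, not in the document: one true SAE in each arm, and k further MA events made serious only by the continuation limb, with none in SA.

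- RR = [(1 + k)/37] / [1/37] = 1 + k
- SE(log RR) = √[1/(1 + k) − 1/37 + 1/1 − 1/37]
- 95% CI = exp(log RR ± 1.96 × SE)

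For k = 3: RR = 4.0; SE = √(0.25 + 1 − 2/37) = √1.196 = 1.094; limits exp(1.386 ± 2.143) = 0.47 and 34.1.

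| k (assumed) | RR | 95% CI |
|---|---|---|
| 0 | 1.0 | – |
| 1 | 2.0 | 0.19 to 21.1 |
| 3 | 4.0 | 0.47 to 34.1 |
| 7 | 8.0 | 1.05 to 60.8 |

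If both arms gained k events, the ratio would stay at (1 + k)/(1 + k) = 1.0. The distortion of the ratio therefore depends on the imbalance between arms. The table shows sensitivity only; the article gives no basis for choosing k.

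**The case against.** The strongest reply is that the text does not say what a critical reader may take from it. Four stronger readings are tempting, and the article supports none of them.

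- **That mild needling intolerance becomes an SAE.** A contraindication is more than poor tolerance, and the examples given are grave. Dizziness and infection are listed as ordinary events, and intolerance appears in 2.2.3 as a plain reason for withdrawal. Stopping on discomfort is followed by assessment and does not by itself rule out further treatment. This objection stands. What survives it is narrower: examples introduced by *such as* do not limit a definition, and an event listed as a common AE can still meet the continuation limb.
- **That 2.8.1 contradicts 2.2.3.** One concerns continued treatment and the other continuing in the study, and ④ does not itself classify events. The relation is a tension, not a contradiction, but it leaves coding unsettled.
- **That the definition stops working after week 4.** Only the continuation limb lapses. The harm limb and its examples still apply up to the last follow-up.
- **That the SAE label decides what the Ethics Committee sees.** Section 2.8.2 sends AEs as well as SAEs, so an event is not lost to that reporting through its label.

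It is also fair that the plan appears to provide an individual listing of SAEs, in which a reader could tell dizziness from a recurrent stroke, and that an SAE ratio with 37 per arm is imprecise under any definition. Events in SA cannot be taken as zero either, since the sham device applies pressure and causes tingling. These points reduce the consequence. They do not repair a definition that the article itself prints. The grading criteria and reporting standards it mentions in 2.8.3 and 2.8.2 are not named there and do not displace that definition.

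**Conclusion.** The point holds in a limited form. The continuation limb is sufficient alone and mixes seriousness with discontinuation. It can class non-serious, treatment-limiting events as SAEs, has no meaning after week 4, and is in tension with 2.2.3 (1)④. Until these passages are reconciled, the SAE risk ratio in 2.8.3 may be partly a comparison of treatment-limiting events.

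The size and even the presence of a bias between arms are unknown. The direction towards more SAEs in MA is plausible because only those needles penetrate, but it is not established. No multiplier can be defended, because the article gives neither an SAE rate nor a rate of stopping treatment. The RR of 4.0 rests wholly on assumed counts and shows only that a few events matter at 37 per arm. The primary analysis and the sample size are unaffected.

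**What to change.** 1. In 2.8.1, define seriousness by the outcome of the event, and apply that definition unchanged from the first session to the 3-month visit. The two existing examples can stay.
2. Remove the treatment-continuation limb from the definition.
3. Add a separate field to the adverse event form, *led to stopping treatment: yes/no*, and report it by arm beside the SAE results in 2.8.3. Information on tolerability is then kept and shown as such.
4. Reconcile 2.8.1 with 2.2.3 (1)④ so that an event is classified the same way under both.

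This changes classification only. Who stops treatment, and when, remains a clinical decision on which this point takes no position.

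The cost is a wording change in two sections and one CRF field. A small downside is that explicit outcome criteria may lead to a few more SAE reports during follow-up.
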